## Abstract

**Background:** A recent analysis showed that plasma iron concentrations decline rapidly from birth in Gambian infants, irrespective of sex or birthweight, to concentrations well below normal expected values for iron-replete children older than two months of age (typically >10 μmol/L). The development and function of neural and immune cells may thus be compromised before the minimum age at which children should receive iron supplementation as per World Health Organisation recommendations.

**Methods:** This study is a two-arm, double-blind, placebo-controlled, randomised superiority trial. Infants will be randomised to receive iron drops (7.5mg/day of iron as ferrous sulphate) or placebo daily for 98 days, to test the impact on serum iron concentrations in healthy, breastfed infants (n = 100) aged 6-10 weeks at enrolment. Participants will be visited daily and supplemented by the field team. Daily health and weekly breastfeeding questionnaires will be administered. Anthropometry, and venous blood and faecal samples will be collected at enrolment and after 98 days of supplementation with serum iron as the primary endpoint. Low birthweight (less than 2.5kg at birth) and infants born prematurely (< 37 weeks) will not be excluded. Formula-fed and infants with any illness will be excluded. An additional study exploring maternal stakeholder perspectives of the intervention will be conducted by means of maternal interviews and four focus group discussions with local stakeholders.

**Discussion:** Most breast-fed Gambian infants have very low circulating iron levels by five months of age. This study will introduce iron supplements much earlier in infancy than has previously been attempted in a low-income setting with the primary aim of increasing serum iron concentration.

**Trial registration:** Clincaltrials.gov (
NCT04751994); 12
^th^ February 2021

## Introduction

In a recent study, rural Gambian infants (n = 317) had serum iron levels far below the reference range in their first year of life
^
1
^. The infants were born with a reasonable endowment of iron despite being born to iron deficient mothers, but following birth there was a rapid deterioration of haemoglobin and ferritin, especially in the fastest growing infants
^
1
^. By five months of age about 95% of the infants had low serum iron concentrations (below 5 umol/L at five months of age) and this continued beyond the first year of life.
Figure 1 combines this data with other published and unpublished data from the same setting confirming that serum iron levels fall far below standard ranges for infants. Serum iron is the source of iron for growing tissues such as neuronal and immune cells
^
2
^.

**Figure 1. f1:**
[figure not shown]
Low serum iron levels in breastfed Gambian infants and pregnant women. Data sources: Reference ranges (shaded green)
^
8
^. Pregnancy (dark green diamonds)
^
9
^. Neonates (yellow diamonds)
^
10
^. Infancy (blue diamonds)
^
1
^. Infancy (red diamonds; analysis of stored samples
^
11
^. Childhood and adulthood (light green diamonds); unpublished analysis from the Keneba Biobank
^
12
^.

During the first three years of life there is rapid myelination especially of the frontal cortex and basal ganglia (motor control)
^
3
^. Infants with iron deficiency can have symptoms that are consistent with impaired hippocampal function, reduced myelination, altered temperament and dopamine metabolism. Iron-deficient infants can present with decreased attention and memory
^
4
^ with deficits in visual and auditory systems as well as altered temperament, and social and emotional behaviours
^
5
^. A large body of evidence both from humans and animal models indicates that iron deficiency in early life can alter the brain and nervous system
^
6
^. Since circulating iron is the only iron source for circulating immune cells it may be anticipated that immune function, including appropriate responses to childhood vaccination, might also be compromised
^
7
^.

Therefore, the goal of this pilot study is to introduce iron supplements to breastfed babies much earlier in infancy in a low-resource setting with the aim of improving serum iron concentration. If this trial is successful, we plan to conduct a larger trial that includes behavioural, cognitive and immune assessments.

### Study objectives

The primary objective is to measure the impact of daily iron supplements for 98 days starting at 6–10 weeks of age on serum iron concentration at the end of the intervention in breastfed Gambian infants. The secondary objectives are to determine if iron supplementation at this age will affect: (1) the duration of exclusive breastfeeding, (2) growth, (3) pathological processes in the gut, and (4) the frequency of adverse events.

Additionally, a qualitative study will assess the acceptability of the iron supplementation efficacy trial. The supplementary objectives are to:

a) Explore mothers’ (the main care providers) perspectives on the acceptability of iron supplementation in their young, breast-fed infants through in-depth interviews.b) Explore the acceptability of iron supplementation in young, breast-fed infants through focus group discussions with local stakeholders.c) To integrate the quantitative and qualitative clinical intervention outcomes to explore the acceptability of iron supplementation in young, breast-fed infants.

## Protocol

### Study design and site

This is a two-arm, double-blind, placebo-controlled, individually randomised trial comparing children (n=100) who receive daily supplements with or without iron (7.5mg/day of iron as ferrous sulphate) for a duration of 98 days.

The study is based at the Medical Research Council (MRC) Unit the Gambia (MRCG) at the London School of Hygiene and Tropical Medicine (LSHTM) (MRCG@LSHTM). The study operates out of the MRCG@LSHTM Keneba field station and the Jarra Soma Regional Hospital in the Lower River Region. Study participants will be recruited from the Soma region of The Gambia through community-based clinics and birth attendants.

### Participants

**
*Recruitment, informed consent, and screening.*
** Healthy infants from the local communities will be identified at six to ten weeks of age. The eligibility criteria will be explained to their parents/guardians, and they will be invited to join the study by providing consent for their infant. Participants must meet all the inclusion criteria and none of the exclusion criteria to be eligible to participate in the trial.

**Informed consent**

Individual written consent for the study will be sought. Field workers will be trained to explain the project in full detail to the eligible participants’ parents/guardians, covering all aspects of such study as laid out in the ‘Participant Information Sheet’ (see
*Extended data*). Literate parents will be given the Participant Information Sheet whilst illiterate parents will have the full Participant Information Sheet read to them in a language they understand. Illiterate consenting subjects will require an independent literate witness. Any questions that arise will be answered by the field workers and parents/guardians will be given the possibility to obtain further clarifications and explanations by speaking to one of the study investigators. All potentially eligible infants whose parents/guardians provide consent will be invited to a baseline visit.

### Eligibility criteria

**
*Inclusion criteria.*
** Inclusion criteria are: infants (male or female) aged between 6–10 weeks. Infants must be exclusively breastfed with plans to continue breastfeeding through six months of age. Parents/guardians (with the participant) must reside in the study site area and be able and willing to adhere to all protocol visits and procedures. Infants must be healthy with no current illness and no chronic health problems. Informed consent must be obtained from the participants parent/guardian. Low birth weight infants (less than 2.5kg at birth) or infants born prematurely (less than 37 weeks) will be included.

**
*Exclusion criteria.*
** Exclusion criteria include formula fed infants or those whose parents/guardians are planning to use commercially available infant formula before six months of age. Infants may not have acute illness, however, once acute illness is resolved, participants may be re-revaluated for eligibility. Infants with fever (a body temperature greater than 37.5°C or mother report of fever) within three days prior to randomisation will be excluded (once fever/acute illness is resolved, participant may be re-revaluated for eligibility). Infants of parents/guardians unwilling for their infant to avoid the ingestion of supplements or herbal/other traditional medications during the study period will be excluded. Infants with any history of, or evidence for, a chronic clinically significant disorder or disease (including, but not limited to, immunodeficiency, autoimmunity, congenital abnormality, bleeding disorder, and pulmonary, cardiovascular, metabolic, neurologic, renal, or hepatic disease), self-reported history suggestive of meningitis, seizures, Guillain-Barré syndrome, or other neurological disorders, or any condition that in the opinion of the investigator may compromise the safety or well-being of the participant or compromise adherence to protocol procedures, will be excluded.

### Baseline

Once parents/guardians of the infant have signed the informed consent document, the infants will be physically examined by a study nurse and, if the infant is considered as generally healthy, their height and weight will be measured. At baseline, a 3 ml blood sample will be collected (0.5 ml in EDTA tube and 2.5 ml in serum tube) to assess the full blood count (including reticulocyte count) and to determine iron status. Parents/guardians of participants will be asked to place nappies inside-out on participants the morning before the baseline or endline visits. Faecal samples will be collected from the nappies by field workers using a spatula. This will be put in universal containers and kept in a cold box. Both blood and stool samples will be transported to the Keneba laboratory for processing and storage into -80°C within 4hrs after collection. Participants who do not pass stool will be provided with labelled universal containers and a cold box to collect faecal samples. The sample will be transported and processed by the field supervisor. This will be stored immediately into a −20°C freezer in Jarra Soma. Frozen stool sample will be transported and stored in Keneba at −80°C. Infants with haemoglobin concentration < 70 g/L will be referred to the regional health centre for treatment according to national guidelines. For safety purposes, all infant’s health will be monitored by the field workers for two weeks post supplementation. See
Figure 2 for the full study scheme.

**Figure 2. f2:**
[figure not shown]
Pilot study schematic.

### Randomisation and blinding

Participants will be individually and randomly allocated on a 1:1 ratio to daily oral supplementation for 98 days with either iron or placebo. A randomization code will be produced in R software (see
*Extended data*) and incorporated in REDCap software by the database manager (who is not part of the field team), with support from the trial statistician. The data manager, all investigators, and the entire study team are blinded to the intervention codes. The randomisation module will be protected by the RedCap “user access privilege” function to ensure that the randomization codes are not changed. Each participant will be assigned to a unique intervention code that is only known by the dedicated person independent from the study. This will prevent the unblinding of the entire study should there be a request for unblinding from the Data Safety Monitoring Board (DSMB) in the case of a serious adverse event. A list of identification numbers will be generated in advance by the MRCG@LSHTM data team with the oversight of the database manager. The study identification number (Study ID) will comprise a three-letter study code (IRN), a three-digit unique number (e.g. 001–140) and a check letter (e.g. A-Z). Every consented participant will be assigned a Study ID (e.g. IRN001X). At the end of the baseline visit, after eligibility has been fully established, the database manager/sub-investigator will allocate each Study ID to one of the six intervention codes (pre-labelled bottles of either intervention or placebo) using the randomisation module on Redcap. 

We will use permuted block randomisation with a fixed block size of six (three replications of two treatment groups within each block) to produce a list with the Study IDs. To assist in the blinding to treatment, the six numbers (1–6) will be linked to two intervention groups, so that each intervention (iron or placebo) will be replicated 3-fold within a permuted block, and arbitrarily assign the alphabetical letters to intervention groups (e.g., 1, 4, 5 indicate iron; 2, 3 and 6 indicate placebo).

A pharmacist will pre-label and re-bottle the intervention and placebo using the randomisation codes 1–6. Only the pharmacist (an independent person not involved in the trial) will know the interpretation of the randomisation codes (1–6). The codes will be put in a sealed opaque envelope and stored in a locked box. Once a participant’s eligibility to participate in the trial has been fully established and confirmed in REDCap, the participant will automatically be allocated to the next available treatment code. This treatment code with the corresponding study ID will be sent to the study nurses via email for labelling and dispensing to the field workers.

### Interventions

Supplements will be administered as drops from a liquid formulation containing either iron (7.5mg contained in 0.5mL) or its placebo (sorbitol solution USP 70%, an inactive ingredient in the iron supplements). The intervention and placebo will be issued in identical dark brown plastic bottles. The ferrous sulphate (intervention) and sorbitol (placebo) will be manufactured such that they are identical in terms of taste and appearance thus, allowing robust allocation concealment. Infants will be visited in their homes daily for 98 days by the field workers who will administer the drops. Products will be stored at ambient temperature (15–30˚C), away from direct sunlight, at both the MRCG@LSHTM Keneba Field Station main store and Jarra Soma health clinic in a locked room. The procured products have a 12-month shelf-life and expiry dates will be checked by the sub-investigator during study implementation.

### Follow up

The final study visit will be on Day 99 after 98 days of supplementation. Procedures for blood and faecal collections and storage and anthropomentry will be as per baseline. 

An early termination visit may occur because of a participant’s voluntary withdrawal, trial team decision, or at the discretion of the DSMB. Apart from the safety evaluations, no other evaluations required for the final study visit will be done.

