### Sample size

We intend to enrol 100 infants in the trial, which will be sufficient to have 80% probability that, if the true increase in geometric mean serum iron concentration in the iron group increases by 70% or more relative to the control group, the 95% confidence interval for the ratio would exclude zero (with the additional assumptions that the variance of log
_e_ serum iron concentration [in µmol/L] is 0.76 for each group
^
13
^; 10% of infants in the iron group stop taking iron supplements in the course of the intervention period; and the percentage of infants in the control group who stop taking placebo supplements is negligible) (
Figure 3). In absolute terms, an increase by 70% corresponds to a change of geometric mean serum iron concentration of 3.0µmol/L, assuming that this concentration is 4.3µmol/L in the placebo group (as observed at Day 0 in Armitage
*et al.* 2019
^
1
^), so that it will have increased 7.3µmol/L in the iron group. We consider intervention effects below 3.0 µmol/L (absolute group difference in geometric means) to be unimportant from medical and public health points of view.

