### Statistical analysis

**
*Main study.*
** Statistical analyses will be performed using R studio and STATA software. Intervention groups will be described using conventional summary statistics (e.g., means or counts with standard deviations, medians with 25- and 75-centiles). The primary analysis concerns the effect of intervention on serum iron concentration at Day 99 (i.e., 98 days of intervention with a 1-day wash-out period after administration of the last supplement, assuming that a transient increase in serum iron concentration following iron supplementation will disappear within this period), adjusted for serum iron concentration measured at baseline. Continuous outcomes will be analysed by linear regression, with transformation of the outcome as needed to normalise the distribution of residuals. Analysis will be by modified intention-to-treat, i.e., all infants who were randomised and who received at least one supplemental dose will be included. We also plan to perform per protocol analysis (i.e., to assess the efficacy that can be attained under controlled conditions) to determine the sensitivity of our modified intention-to-treat analysis. To account for missing data, we will use multiple imputations. In secondary analyses, we will adjust for any group imbalances that may occur in prognostic variables measured at baseline. Serum iron concentrations are known to undergo diurnal fluctuation and they are known to be reduced in inflammation
^
18
^. Thus, to account for these effects, we will also conduct secondary analyses with adjustment for the time of blood collection and for plasma concentrations of C-reactive protein and alpha-1 acid glycoprotein at the time of blood collection.

Group differences in adverse events will be analysed using negative binomial regression. In this analysis, we will count adverse events as the number of days with adverse events divided by the total number of days that the infant was observed during the intervention period. In the analysis of diarrhoea, we will count an event if the parent/guardian reported three or more fluid stools (as indicated by a WHO stool chart) in the previous 24-hour recall period
^
19
^. To produce conservative effect estimates, analyses of adverse events will be per protocol.

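### Infants ended early by the trial team or DSMB get no Day 99 serum iron measurement even if the parent still consents, so the primary endpoint is avoidably missing for infants in the modified intention-to-treat set

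*Protocol article*

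**What the plan says.** The Follow up section of the protocol article puts the final visit on Day 99, with blood, stool and anthropometry as at baseline. It then names three routes to an early termination visit: voluntary withdrawal, a decision of the trial team, and the discretion of the DSMB. One rule covers all three: "Apart from the safety evaluations, no other evaluations required for the final study visit will be done". Nothing in the article brings such an infant back for the scheduled Day 99 sample.

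The Outcomes section makes serum iron on Day 99 the primary endpoint. The Statistical analysis section defines the modified intention-to-treat set so that "all infants who were randomised and who received at least one supplemental dose will be included", and it handles missing data by multiple imputation. A per-protocol analysis is planned as a check.

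The Sample size section assumes that "10% of infants in the iron group stop taking iron supplements in the course of the intervention period" and that stopping of placebo is negligible. It names no loss of outcome data.

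The Withdrawal of participants section speaks of withdrawing participation or consent, but does not say that outcome collection differs between the two.

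**The concern.** This is a stated rule, not a detail left to another document, and no analysis plan can recover blood that was never drawn. When a parent withdraws consent, the missing value may be unavoidable. When the trial team or the DSMB ends participation, the parent may still be willing, and the protocol itself then creates the gap.

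What is at stake is the quantity estimated. A modified intention-to-treat comparison should carry the outcomes of infants who did not complete the supplements. If those outcomes are missing and are imputed under missing-at-random, the donors in the iron arm are mainly infants who kept taking iron. The result may then drift towards the effect in continuers while still being labelled intention-to-treat.

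**Working it through.** **Inputs, all from the Sample size section except allocation.**
- Total: "We intend to enrol 100 infants in the trial", allocated 1:1 (Randomisation and blinding), so 50 per arm.
- Power 80%. Two-sided alpha 0.05 from the 95% confidence interval, worked on the log scale.
- Geometric mean ratio 1.70; ln 1.70 = 0.5306.
- Variance of log serum iron 0.76 per group.
- 10% of the iron arm stop supplements; placebo stopping taken as 0%.
- Placebo geometric mean 4.3 µmol/L.

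**Step 1. Reproduce the plan's sample size.** Keep the 10% who stop in the analysis, with the placebo mean:
- Diluted ratio = 0.9 × 1.70 + 0.1 × 1.00 = 1.63; ln 1.63 = 0.4886.
- n per arm = 2 × (1.960 + 0.842)² × 0.76 / 0.4886² = 50, so N = 100.
- SE = √(0.76 × 2/50) = 0.174; z = 0.4886 / 0.174 = 2.80; power = Φ(2.80 − 1.96) = 80.0%.

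The plan's figure is reproduced. The other readings tried do not give 100:

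| Treatment of the 10% | N |
|---|---|
| Ignored | 86 |
| Dropout, both arms inflated | 96 |
| Dropout, iron arm only inflated | 91 |
| Diluted on the log scale (0.9 × ln 1.70) | 106 |

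So the stated N is consistent with infants who stop iron being measured and showing no effect. The section does not say this; the arithmetic implies it.

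**Step 2. Upper bound for the shift.** The article gives no early-termination rate, so vary the share of the 10% who are terminated and unmeasured, with no terminations on placebo. Expected ratio among measured infants = (0.9 × 1.70 + stoppers still measured) / (0.9 + stoppers still measured).

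| Share of stoppers unmeasured | Measured, iron v placebo | Ratio | Difference, 4.3 × (ratio − 1) | Power |
|---|---|---|---|---|
| None | 50 v 50 | 1.63 | 2.7 µmol/L | 80.0% |
| Half | 47.5 v 50 | 1.66 | 2.9 µmol/L | 82.1% |
| All | 45 v 50 | 1.70 | 3.0 µmol/L | 84.2% |

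Check of the last row: SE = √(0.76 × (1/45 + 1/50)) = 0.179; 0.5306 / 0.179 = 2.96; Φ(2.96 − 1.96) = 84.2%. Imputing the five missing infants from the continuers in their arm gives the same expected ratio: 0.9 × 1.70 + 0.1 × 1.70 = 1.70.

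**Step 3. Size relative to sampling error.** ln(1.70/1.63) = 0.042, and 0.042 / 0.174 = 0.24 of one standard error. This SE ignores the planned adjustment for baseline serum iron. The article gives no baseline to Day 99 correlation. At an assumed 0.5 the SE would be 0.174 × √0.75 = 0.151 and the shift 0.28 of one standard error, so the order of magnitude does not change.

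**The case against.** The strongest reply is that stopping supplements and leaving the study are different events. No section says that an infant who stops supplements is terminated. The Data and safety monitoring section withholds supplements for seven days for listed conditions, without ending participation. An infant who stops iron but stays in the study would have the ordinary Day 99 visit. This stands, and it rules out several stronger readings that a reader might infer:

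- **That the Follow up rule contradicts the sample size.** It does not. The 10% concerns supplements; the rule concerns participation. The article does not say how far the two overlap.
- **That missing outcomes will fall almost only in the iron arm.** The plan assumes differential stopping of supplements, not differential missing outcomes. Nor does it say that termination is tied to illness or tolerance.
- **That the rule defeats the modified intention-to-treat analysis.** Multiple imputation keeps the infants in the set. How far imputed values lean towards continuers depends on a model the article does not give and need not give.
- **That the rule moves the result across the plan's importance threshold.** The plan sets its undiluted effect, 3.0 µmol/L, equal to that threshold. Any dilution therefore falls below it and removing dilution returns to it, which says nothing about how likely or large the bias is.
- **That power is lost.** It is not, on the plan's figures. Power would fall only if other infants were lost as well as the dilution: 45 v 50 at ratio 1.63 gives 77.9%, on an assumed loss.

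It is also fair that some withdrawn infants could not be sampled under any rule. What survives is the narrower point: by rule, infants ended by the team or DSMB are not sampled even when the parent still agrees.

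**Conclusion.** The point holds in this limited form. The early-termination rule makes the primary endpoint missing for some infants whom the primary analysis must include, and part of that missingness is avoidable. The number affected is unknown and may be very small.

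The move from 1.63 to 1.70, about a quarter of one standard error, is the most that the plan's own 10% allows. It requires that every infant who stops iron is terminated and unmeasured, that none of them has any iron effect, that no placebo infant is terminated, and that imputation treats them as continuers. Relaxing any of the first, second or fourth shrinks it. A termination rate above 10% in the iron arm would enlarge it, but the article gives no ground for assuming one. The harm is to what is estimated, not to power.

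**What to change.** Amend the Follow up section to distinguish three states: supplements stopped, participation ended by the trial team or DSMB, and consent withdrawn. For the first two, seek the scheduled Day 99 blood, stool and anthropometry from every infant whose parent still agrees. Keep the safety-only rule for parents who decline. This changes outcome collection only, not when supplements are stopped.

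For infants still missing, add a sensitivity analysis that imputes iron-arm infants who stopped from the placebo distribution, unless the statistical analysis plan already has one. It needs no new visits.

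The cost is a short amendment with its ethics review and a few extra samples. Its reach is limited: the Study status section reports all 100 infants recruited by November 2021 and the last follow-up due in March 2022, so the collection change helps only infants not yet at Day 99. For the rest, report the number ended early by arm and route alongside the sensitivity analysis.
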